#### Phase I: development phase

This is a cohort study to determine the variables and potential classes to be
included in a casemix classification, based on individual episodes of care across
inpatient (hospice and hospital) and community settings. An ‘episode of
care’ starts when a patient is admitted to inpatient services or begins to
receive specialist palliative care from a community-based or outpatient service,
and ends when a patient is discharged from that service or dies. The median
duration of an episode of care is expected to be under 14 days in inpatient and at
a median of 72 days in community settings.^18^

Phase I was conducted between 31 July 2015 and 30 September 2016 and follow-up
ended on 30 November 2016. Data were collected from clinicians through
surveys, including demographic/clinical data, episode start/end data, patient
attributes that predict palliative care resource consumption (eg, phase of
illness, functional status and problem severity as identified in the Australian
casemix classification study^13 14 16^), plus information on patient-level resource use (staff activity and
clinical services) in specialist palliative care settings.

#### Phase II: validation phase

This phase is a mixed-methods cohort study with a concurrent nested design:^19^
Quantitative main component—prospectively collect data from
patients, caregivers and clinicians on palliative care needs, concerns,
outcomes and resource use.Qualitative nested component—longitudinal interviews with a
subsample of participants to understand care provision in each setting
and transitions between settings.

Phase II will be conducted between 1 November 2016 and 30 April 2018, with
follow-up ending on 31 May 2018. The same variables and measurements
as phase I will be collected from clinicians. Additionally, patient/caregiver
participants will provide data on symptoms/concerns, experience of care and their
use of services, and will be followed through all episodes of care from
recruitment to death or the end of this study. A post bereavement survey will be
conducted with caregivers where appropriate to identify symptoms/concerns
immediately prior to death and support needs after death.

### Participants

#### Phase I: development phase

All adults (≥18 years) receiving specialist palliative care newly admitted
in 10 participating sites during the study period (two sites providing hospital
advisory services, one providing community-based service only, six providing
hospice inpatient and community-based services, one providing hospital advisory
and community-based services) were included, regardless of primary diagnosis. We
selected these sites with the aim of ensuring a representative sample in terms of
population demographics (age distribution, ethnicity, socioeconomic status and
rural/urban composition). Written informed consent was taken by a qualified member
of the research or clinical team. This phase included individuals with limited,
fluctuating, diminishing or lack of capacity, vital to ensure that any casemix
classification is applicable to all palliative patients, not just those able to
consent. It is recognised that a high proportion of those have impaired capacity,
and these patients may need palliative care and resources most.^20–23^ Therefore, if the
clinician assessed that the patient did not currently have the capacity to give
consent, assent was sought from an accompanying family member, or failing that, a
staff member to whom the patient was known. Where a formally appointed power of
attorney existed, this took precedence.

#### Phase II: validation phase

All adults (≥18 years) receiving specialist palliative care newly admitted
from 14 sites during the study period (participating sites in phase I, but
extending to four additional sites to increase recruitment) will be eligible,
regardless of primary diagnosis. Additional sites were accepted if they could
contribute to maintaining or extending representativeness in terms of population
demographics (age distribution, ethnicity, socioeconomic status and rural/urban
composition). Written informed consent will be sought from eligible patients (and
their family caregivers) at the outset, including advance consent for study
follow-up if capacity is lost. This study is of minimal risk with participants not
exposed to undue harm.^24^

For both phase I and II, a list of study sites can be obtained via https://www.kcl.ac.uk/nursing/departments/cicelysaunders/research/studies/c-change/c-change.aspx.

Since transition of care is important for casemix, patient participants who
transfer between settings (and caregiver participants) will be followed up. We
will verbally confirm continuing consent with each participant when making such
contact. If capacity of patient participants is lost, we will seek advice from a
personal consultee on whether the patient should remain in the study to verify no
change of decisions has been expressed by the patient prior to loss of capacity.
On recruitment, participants will be asked if they are willing to be interviewed
at a later stage. To capture variation in age, gender, diagnosis and geographical
location, we will purposively select 20–25 patients and family caregivers
with at least two transitions of care for face-to-face interviews. Each
semistructured interview will last 40 min, but will be guided by each
participant. In order to provide information on how care transitions might be
better negotiated to improve outcomes and experiences, the interviews will cover
communication, coordination of care, information/support needs, discharge planning
and experience of transitions.

### Outcome

The outcome is cost of specialist palliative care (including per diem cost, per phase
cost, and total episode cost) captured by: (1) staff activity matrix in both the
development and validation phase, (2) the Palliative care Resource Use Score (PRUS)
in both phases and (3) Palliative Client Services Receipt Inventory (Pall-CSRI) in
validation phase only.

#### Staff activity

At every contact, nurses, doctors and allied health professionals will record the
time spent on face-to-face and phone contacts, and patient-level administrative
time per shift using the staff activity matrix paper version (table 1). Staff training and site feedback of
activity data were conducted regularly to improve and optimise data quality.

**Table 1 T1:** Staff activity matrix (each box is completed in units of 5 min, from
0 up to 120 min)

Staff time (mins)	Patient	Family/carer	Professional (internal)	Professional (external)
Face-to-face/phone time				
Administrative time				

#### Palliative care Resource Use Score

PRUS is a questionnaire specifically designed to capture palliative care resource
use in a standardised way. It will be collected by the staff at change of
‘phase of illness’^25 26^
and at the end of each episode by recording the following information for the
phase which has ended:Level of professional input (eg, registered nurses, specialist palliative
nursing staff, palliative doctors and social workers) and whether this
met patient/family needs.Level of ‘out-of-hours’ services by professional
designation.Equipment, high-cost drugs, diagnostic tests and medical imaging. Within
PRUS, the member of staff is asked to indicate whether or not equipment,
high-cost oral/transdermal medications, injectable
medications/interventions and medical imaging or tests were received by
the participant, from a list derived from prior work to identify these
options.Any unmet needs which provide insight into any gaps between needs and
provision, as identified by a member of staff.^27–29^ When completing PRUS, the member
of staff is asked to estimate retrospectively if there were any unmet
needs (yes/no) in the care provided by healthcare assistants, registered
nurses, palliative medicine doctors and allied healthcare professionals.
This member of the staff is also asked whether there were any unmet needs
in out-of-hours care, and whether the equipment provided met the
patient’s needs. If there were unmet needs identified in any of
these areas above, a free text field is provided to specify these unmet
needs.

#### Palliative Client Services Receipt Inventory

The Pall-CSRI is a patient/caregiver completed inventory of palliative care
services received, and adapted from those used with palliative care
populations.^30^ It takes approximately
20 min to complete and collect retrospective information about the use of
health/social care services, medication, living situation, income, employment and
benefits, plus informal care. The Pall-CSRI will be collected once every three
months or at the end of each episode of care, whichever is earlier in the
validation phase.

In the development phase, only direct care costs will be calculated but not
productivity losses.^31^ Direct care cost
refers to all costs due to resource use that are completely attributable to the
use of a healthcare intervention or illness, which can be split into direct
medical costs (the cost of a defined intervention and all follow-up costs for
other medication and healthcare interventions in ambulatory, inpatient, nursing
care, home or other relevant settings) and direct non-medical costs (eg,
transportation costs and additional paid caregiver time).^32^ In the validation phase, we will use the same health
services costing perspective as in the development phase, but informal care costs
are also considered to be in-scope and will be analysed separately, hypothesising
that informal care costs are (1) greater in those with unmet needs, and (2)
greater in those with non-cancer conditions. The costs of each resource item will
be calculated by combining the resource use data with appropriate unit cost
obtained from recognised sources including the annual compendium produced by the
Personal Social Services Research Unit,^33^
prices on the National Health Service (NHS) supply chain website http://www.supplychain.nhs.uk, British national formulary^34^ and NHS reference costs.^35^ The focus will be on staff time—the
main resource in palliative care documented in a variety of settings and
countries.^36–38^ We will
attribute costs according to a standard costing methodology adopted from the
current NHS costing principles.^39^

### Predictors (casemix criteria)

Proposed cost predictors can be categorised into three groups: (1) predictors
collected from clinicians, (2) predictors collected from patients/family caregivers
and (3) model of care.

#### Predictors collected from clinicians

In both the development and validation phases, clinicians will record demographic,
clinical and episode start administrative data. Episode end data will be collected
at the end of each episode of care. Casemix data include phase of illness (stable,
unstable, deteriorating, dying), functional status (measured by Australia-modified
Karnofsky Performance Status (AKPS)), dependency (Modified Barthel Index), problem
severity (Integrated Palliative care Outcome Scale—IPOS staff version) and
caregiver needs (table 2). The measures are
available directly from phase of illness (www.pcoc.org.au), AKPS,^40^ Modified Barthel Index^41^ and IPOS (www.pos-pal.org), respectively. Phase of illness will be assessed
daily for people receiving inpatient care and at each face-to-face contact basis
for those receiving community-based care. Other variables including AKPS, Modified
Barthel Index, IPOS staff (and caregiver needs when feasible) will be collected at
the start of episode, end of episode and at change of phase of illness.

**Table 2 T2:** Data from clinicians in both development phase and validation phase

Type of data	Proposed cost predictors
Demographic data	Age
	Gender
	Postcode
	Ethnicity
	Marital status
	Living circumstances
	Need for interpreter
	Setting of care
Clinical data	Primary diagnosis
	Secondary diagnoses
	Comorbidities
Episode start and end data	Episode start date
	Episode end date
	Endpoint of episode (discharged or died).
	Discharge destination, if discharged
Key casemix	Phase of illness at start of episode
	Functional status (AKPS)
	Dependency (Modified Barthel Index)
	Problem severity (IPOS staff version)
	Family/caregiver needs

AKPS, Australia-modified Karnofsky Performance Status; IPOS, Integrated
Palliative care Outcome Scale.

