#### Predictors collected from patients and family caregivers

Variables (table 3) will be collected in
the validation phase from patients/caregivers using face-to-face/telephone
contacts and postal questionnaires according to their preferences.
IPOS patient version and Distress Thermometer will be collected from
patients at the start of episode, at change of phase of illness and at the end of
episode. Views on Care and Short-Form Health Survey V.2.0 (SF-12v2) will be
collected at the start and end of each episode of care. Selected questions
capturing experiences of integrated care^42^
will be collected at the end of episode only.

**Table 3 T3:** Predictors collected from patients and family caregivers in validation phase
only

Data collection from patients	Data collection from family caregivers
IPOS patient version	Basic demographic information
Distress Thermometer	Distress Thermometer
Views on Care	Two caregiver questions
SF-12v2*	Zarit six items
Patient experiences of integrated care	

*The measure could be completed by a family caregiver if the patient is
too unwell to complete.

SF -12v2, Short-Form Health Survey V.2.0.

All caregiver- reported measures will be collected at the start of episode, at
change of phase of illness and at the end of episode. Where phase length exceeds 4
weeks, data collected from patients (and caregivers) will be captured as a change
of phase. If the patient is transferred to an out-of-scope inpatient setting, we
will follow up with the patient when he or she gets home and
retrospectively collect minimum information about this episode of care.

If the patient is deceased, data such as SF-12v2 and Pall-CSRI will be collected
from the participating caregiver three months after death by postal
questionnaire, along with the bereavement support information and contacts. The
time between death and the postal questionnaire may influence caregivers’
willingness to share their views; shorter periods possibly being too upsetting to
contemplate involvement.^43^ There is mixed
evidence of the best time to make contact with potential participants for
follow-back surveys^44 45^ and 3–4
months post bereavement is considered acceptable by bereaved families.^30^

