### Model development

The distribution of casemix criteria (cost predictors) in the participant population
will be described based on phase of illness, functional status and problem severity,
using parametric or non-parametric statistics, as appropriate. In order to reduce the
number of cost predictors, we will initially use univariate analysis to explore the
association and strength of association between casemix criteria and cost of the
episode of care (quantifying cost by per diem cost, per phase cost and total cost of
episode). We will use generalised linear model (multivariate regression model) to
select variables that will then be applied in a hierarchical manner to form a
branching classification in which each cost driver is incorporated only once.

We will select variables according to how much of the predictive error
(R^2^) each variable predicts and the related P value. After each
bootstrap iteration, we will rank the variables according to these two criteria and
remove the weakest (non-significant) predictor. Variables shown in tables 2 and 3 and the newly created
categorical variable representing ‘model of care’ will be initially
entered into the models and then non-significant predictors removed at each iteration
using a Bootstrap subsampling strategy. We will create dummy variables to enable each
level of phase of illness and model of care (categorical variables) to be assessed
individually. Internal validation will be conducted by using such methods as
bootstrapping or cross-validation to quantify any optimism in the predictive
performance (calibration and discrimination) of the developed classification.

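### Four items known only when an episode ends are entered as candidate cost predictors, so episode length can leak into the cost models and inflate their apparent performance.

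*Protocol article*

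**What the plan says.** The Outcome section defines three cost outcomes: per diem, per phase and total episode cost. The stated purpose of the classification is to predict costs.

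Table 2, under Predictors collected from clinicians, has the column heading "Proposed cost predictors". One group of rows holds the episode start and end data: start date, "Episode end date", the row beginning "Endpoint of episode (discharged or died", and "Discharge destination, if discharged". The text above the table gives the timing: "Episode end data will be collected at the end of each episode of care".

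Table 3, titled as predictors from patients and family caregivers in the validation phase only, includes patient experiences of integrated care. The text says that these questions "will be collected at the end of episode only".

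Model development then fixes what goes into the regression. "Variables shown in tables 2 and 3 and the newly created" model-of-care variable are to be initially "entered into the models and then non-significant predictors removed at each iteration", with variables ranked by R-squared and P value. No section excludes the items known only at episode end.

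**The concern.** A model meant to predict the cost of an episode should use what is known when the episode, or the phase, begins. End date, endpoint, discharge destination and the end-only experience measure become known when the cost has already been incurred. The dates matter most. Both start and end date are candidates, so a linear model can form their difference, which is episode length. Length multiplies per diem cost to give total cost, and it divides total cost to give per diem cost.

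A rule that ranks by R-squared and P value rewards this kind of association. Three things are at stake:

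- Genuine casemix criteria could be displaced, and the classes could depend on information that is not available when care is planned.
- The safeguards in the plan would not show it. Bootstrapping and cross-validation measure overfitting, not leakage. Phase II collects the same clinician variables, so the inflation would recur there and look like successful external validation.
- Statistical analysis methods adopts or refines the Australian classification if the same five criteria prove most predictive. None of those five is an end-of-episode item. A leaked variable that ranks high could be counted as disparity and lead to a new classification for the wrong reason.

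**Working it through.** **Count of candidates.** Table 2 has 20 items, Table 3 has 9, and model of care adds 1: 20 + 9 + 1 = 30. Four of the 30 can be known only at or after the end of the episode. Three are in Table 2 (end date, endpoint, discharge destination) and bear on both phases. One is in Table 3 (experiences of integrated care) and bears on phase II only.

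**Algebra.** Length = end date − start date. Total cost = per diem cost × length, so log total cost = log length + log per diem cost. The direction of the leak into total cost follows from this and needs no assumed figure.

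**Size, as an illustration.** The document gives no SD for cost or length, and it disputes no figure of its own here, so there is no stated result to reproduce. Inputs:

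- From the document: median length under 14 days for inpatients (14 used) and 72 days in the community; phase I starts from 31 July 2015 to 30 September 2016 (427 days); follow-up to 30 November 2016 (488 days from the first start).
- Assumed: log-normal length with SD of log length 0.8 to 1.2; SD of log per diem cost 0.4 to 1.0; the two independent; start dates uniform.

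Results from simulation, as the share of the variance of log total cost explained:

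| Entered linearly | Episodes cut at end of follow-up | Not cut |
|---|---|---|
| Start and end date | about 28% to 64% | about 26% to 57% |
| End date alone, inpatient | about 0.5% to 3% | up to 6% |
| End date alone, community | about 2.5% to 9% | up to about 33% |

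**Added to a baseline model.** In a second simulation, start-of-episode casemix was set to explain 13% of log total cost, SD of log length ran from 0.6 to 1.2, and episodes were not cut. Adding both dates raised R-squared from 0.13 to between 0.32 and 0.62, a factor of about 2.5 (0.32/0.13) to 5 (0.62/0.13). On the raw cost scale it rose from 0.03–0.10 to 0.20–0.83. Start date alone added nothing.

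**Would the univariate step remove end date?** The development phase allows for 450 × 0.75 × 0.90 ≈ 304 usable episodes per setting. A single predictor then reaches P < 0.05 at an R-squared of about 3.87/(302 + 3.87) = 1.3%, where 3.87 is the 5% critical value of F on 1 and 302 degrees of freedom. End date alone would pass in the community range and in part of the inpatient range.

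**The case against.** The strongest defence is that Table 2 is an inventory of collected data. Its caption speaks of data from clinicians, it includes raw postcode and dates, and it keeps key casemix items in a separate group. That would hold if the table stood alone. The column heading and the Model development sentence that enters the variables of both tables defeat it.

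Other points limit the concern, and they stand:

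- A reader might infer that the classification cannot predict prospectively. That holds only if an end item survives selection. Sample size expects 5 to 8 final variables that must be clinically relevant, so such items may be dropped. The plan does not ensure it.
- A reader might compute that length of stay explains 39% to 90% of total cost, from s²(length)/(s²(length) + s²(per diem)): 0.64/1.64 = 0.39 and 1.44/1.60 = 0.90. That is for log length as a variable. The plan lists two calendar dates, which carry less when entered linearly. In the tree, where each driver is used once, one split on each date is a poor substitute for their difference.
- A reader might compare these shares with the R-squared of 0.13 in Sample size. That is an effect size for powering a test, not a forecast of what the predictors will explain.
- A reader might extend the point to the questionnaires in general. Only one is end-only, and Table 3 items are not collected in phase I.
- A reader might also fault AKPS, Modified Barthel Index and IPOS because the time point used in the model is not fixed. Those measures are taken at episode start as well, and per phase cost needs values at phase change. Which value feeds which model is detail that an article may leave to the analysis plan.

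**Conclusion.** The point holds in a limited form. As written, the plan admits four variables known only at or after episode end into models meant to predict cost, under a selection rule that favours them and with no check that would reveal the leak. Apparent performance may be inflated in both phases, and the classes are not ensured to be assignable when care is planned. The documents do not support saying that this will happen.

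The figure of about 26% to 64% rests on assumed spreads, independence of length and per diem cost, and linear entry of both dates. It concerns total episode cost only. The effect on per diem cost was not quantified and depends on how daily cost varies with length.

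**What to change.** - In Model development, state that episode end date, endpoint of episode, discharge destination and patient experiences of integrated care are not candidate predictors. Keep them as descriptors, and use the dates to compute cost and length.
- Limit candidate predictors to values known at the start of the episode, or at the start of the phase for per phase cost. Measurements at phase change remain usable for per phase cost.
- Edit Tables 2 and 3 so that the four items no longer appear as predictors.

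The cost is one or two sentences and a table edit. Start-of-episode values are already collected, so no new data and no change of sample size are needed. The reported R-squared will be lower, but it will describe prediction from what is known at the time.
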